## Abstract

**Background:**

Anxiety and depressive disorders are highly prevalent disorders and are mostly treated in primary care. The management of these disorders by general practitioners is not always consistent with prevailing guidelines because of a variety of factors. Designing implementation strategies tailored to prospectively identified barriers could lead to more guideline-recommended care. Although tailoring of implementation strategies is promoted in practice, little is known about the effect on improving the quality of care for the early recognition, diagnosis, and stepped care treatment allocation in patients with anxiety or depressive disorders in general practice. This study examines whether the tailored strategy supplemented with training and feedback is more effective than providing training and feedback alone.

**Methods:**

In this cluster randomised controlled trial, a total of 22 general practices will be assigned to one of two conditions: (1) training, feedback, and tailored interventions and (2) training and feedback. The primary outcome measure is the proportion of patients who have been recognised to have anxiety and/or depressive disorder. The secondary outcome measures in patients are severity of anxiety and depressive symptoms, level of functioning, expectation towards and experience with care, quality of life, and economic costs. Measures are taken after the start of the intervention at baseline and at three- and six-month follow-ups. Secondary outcome measures in general practitioners are adherence to guideline-recommended care in care that has been delivered, the proportion of antidepressant prescriptions, and number of referrals to specialised mental healthcare facilities. Data will be gathered from the electronic medical patient records from the patients included in the study. In a process evaluation, the identification of barriers to change and the relations between prospectively identified barriers and improvement interventions selected for use will be described, as well as the factors that influence the provision of guideline-recommended care.

**Discussion:**

It is hypothesised that the adherence to guideline recommendations will be improved by designing implementation interventions that are tailored to prospectively identified barriers in the local context of general practitioners. Currently, there is insufficient evidence on the most effective and efficient approaches to tailoring, including how barriers should be identified and how interventions should be selected to address the barriers.

**Trial registration:**

NTR1912

## Background

Anxiety and depressive disorders are common mental disorders that have a negative impact on everyday functioning, cause great suffering, and incur both high healthcare costs and additional costs associated with production losses [1-3]. The lifetime prevalence of anxiety and depressive disorders in Dutch adults is about 20%, and the 12-month prevalence is 10% and 5% [4], respectively. Most adults who seek help for their anxiety or depressive disorder are treated in general practice [5,6].

In the Netherlands, clinical guidelines are available for both anxiety and depressive disorders for general practice [7-10]. Enhancing guideline adherence is expected to lead to reduction of the burden of disease and improvement of social functioning [11,12]. The management of anxiety and depressive disorders by general practitioners (GPs) is not always consistent with prevailing guidelines. Under-recognition and consequently under-treatment of anxiety and depressive disorders have been reported, where threshold disorders are more likely to be recognised than are subthreshold disorders [5,13-15]. About a quarter and a half of patients, respectively, receive optimal treatment for an anxiety disorder and a depressive disorder in primary care [16,17]. Besides under-diagnosis and under-treatment in some patients, other patients are over-treated with psychopharmacological drugs, while these are not indicated [5,18,19]. Use of effective early interventions in patients with mild problems, which are often based on cognitive behavioural techniques, is more the exception than the rule [20]. The adherence to guideline recommendations is suboptimal because of a variety of factors influencing GPs' recognition and management of anxiety and depressive disorders. These factors are related to (a) patients, such as lack of recognition of having a psychological problem, presentation of physical symptoms, absence of a perceived need for care; (b) GPs, for example, lack of knowledge and skills, attitudes, time, self-efficacy, patient-physician communication; and (c) organisation of care, such as insufficient collaboration with mental health professionals and waiting lists for specialty mental healthcare [21-26]. In addition, some recommendations in the guidelines have less support from research evidence or may be perceived as less attractive.

To improve adherence to guideline recommendations, various implementation strategies can be effective for improving professional performance in healthcare professionals [27]. Many quality-improvement interventions in anxiety and depression care target provider knowledge through education on treatment guidelines and continuous performance feedback or they contain a fixed package of multiple strategies, such as in the Quality Improvement Collaboratives [28,29]. Other interventions in anxiety and depression care target organisation of healthcare delivery, for instance, by involving mental health consultants [22,30]. The strategies show mixed and overall moderate effects on clinical management of depression and outcomes in primary care.

Our hypothesis is that adherence to guideline recommendations, and consequently patient outcomes, will be improved by designing implementation interventions that are tailored to prospectively identified barriers in the local context of GPs [23,25,31-33]. The choice of a study in tailored implementation is based on the assumption that implementation is affected by impeding local factors related to care professionals, the organisation of care, and social factors. Successful implementation is only possible when these barriers are dealt with through an implementation plan tailored to the situation [34]. Different studies have investigated the impact of tailored interventions for behaviour change in GPs, to improve the quality of care, in randomised controlled trials (RCTs) [32]. Because the tailoring methods used in these studies are heterogeneous, there is insufficient evidence on the most effective and efficient approaches to tailoring, including how barriers should be identified and how interventions should be selected to address the barriers. Therefore, we used a pragmatic and flexible approach of tailoring implementation to barriers to change.

This article describes the aims and methods of an RCT to determine the effectiveness of tailored interventions in the implementation of guideline recommendations for the early recognition, diagnosis, and stepped-care treatment allocation in patients with anxiety or depressive disorders in general practice in the Netherlands.

## Methods/design

### Objectives

The primary aim of this RCT is to determine the effectiveness of tailored interventions to improve the implementation of guideline recommendations for the early recognition, diagnosis, and stepped-care treatment allocation for anxiety and depressive disorders in general practice. Secondary aims are to describe the identification of barriers for improving professional performance, the relationship between prospectively identified barriers and improvement interventions selected for use, and the influencing factors and experiences with the strategy. The final aim is to examine the efficiency of the tailored intervention compared to usual care from a societal perspective with a time horizon of six months.

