### Intervention group

#### Tailored strategies

GPs from the general practices randomised to the intervention group will receive interventions that are tailored to prospectively identified barriers in their local context over the course of one year. Methods for tailoring implementation interventions to local barriers vary widely and are often poorly documented [31]. To get insight in the experienced barriers in the early recognition, appropriate diagnosis, stepped-care treatment allocation, and providing of information on the diagnosis and stepped-care treatment options for anxiety and depressive disorders, a semistructured face-to-face interview was carried out with each of the participating GPs by a trained interviewer. For this interview, we developed a checklist based on the main types of barriers to adherence to evidence-based guidelines on anxiety and depressive disorders by GPs [25,28,38]. Based on these main types of barriers, we developed interventions that could solve the barriers. Each interview was documented in a report. Based on this report, experts suggest interventions that may resolve the barriers. These interventions are fed back by telephone to the GP by the same interviewer.

The interviewer calls the GP once every two months to map the implementation process and links this back to the experts. Again, experts suggest interventions or give advice to the interviewer for the next contact with the GP. With a continuous feedback loop between the experts, the interviewer, and the GP, we optimise the tailoring process. All contacts between the experts, the GP visitor, and the GP are reported.

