#### Control group

GPs from the general practices randomised to the control group only received training and feedback (see intervention group).

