#### Economic evaluation

An economic evaluation will be conducted to estimate the cost effectiveness of the tailored intervention from a societal perspective. The between-group difference in costs will be related to the difference in benefits in terms of health-related utilities. This economic evaluation uses the EQ-5D. The cost-utility analysis measures health in quality-adjusted life years (QALYs), derived using the EQ-5D questionnaire [47]. The EQ-5D characterises five health dimensions (mobility, self-care, usual activities, pain, and anxiety/depression), each rated using three levels (no problems, moderate, and severe problems). Responses will be transformed into a health utility score that ranges between 0 = dead and 1 = full health. Health utilities will then be used to calculate the QALYs. This gives a comparison of how many QALYs individuals in each group gained on average as a result of the tailored intervention. Results can statistically be compared to see if there are any differences. The final step of the cost-utility analysis will be to compare the cost of the QALY gains in each group.

The costs of the implementation strategy used will be studied for each practice. These costs are (a) the costs per hour of the GP visitor and experts for the activities during the tailoring process and the one-day training and feedback, (b) material costs for the one-day training, and (c) the costs per hour of the GP related to the implemented interventions. In addition, the difference in healthcare costs related to the diagnostic process will be included, including number of consultations, diagnostic tests, and referrals with diagnostic aims. Healthcare costs will be measured by the TiC-P. The costs will be estimated in line with the Dutch guidelines for cost calculations in healthcare [48].

Apart from costs of the tailored strategy, healthcare costs, and costs of production losses, indirect costs will be measured for both groups related to the severity of anxiety and depressive symptoms, level of functioning, experience with care, and quality of life.

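### The economic aim names usual care as comparator, but both arms receive training and feedback, so the trial can only estimate the cost-utility of adding tailoring

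*Protocol article*

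**What the plan says.** The relevant statements in the protocol article are these.

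- **Aim (Objectives).** The last of the stated aims reads: "examine the efficiency of the tailored intervention compared to usual care from a societal perspective with a time horizon of six months".
- **Arms (Abstract, Methods).** The two conditions are "1) training, feedback, and tailored interventions and (2) training and feedback". Study design confirms that the educational component goes to both arms and tailoring to one only. Under Control group, those practices "only received training and feedback".
- **Contrast (Economic evaluation; Statistical analyses).** The cost difference between the groups is set against the difference in utility-based benefit, and results are to be presented as incremental cost-effectiveness ratios with bootstrapping and acceptability curves.
- **Duration (Tailored strategies).** The intervention arm receives "interventions that are tailored to prospectively identified barriers in their local context over the course of one year", with a call every two months.
- **Costs counted (Economic evaluation).** Strategy costs include "the costs per hour of the GP visitor and experts for the activities during the tailoring process and the one-day training and feedback". No calendar limit is given.
- **Benefit window (Secondary outcomes, In patients).** EQ-5D and the cost questionnaire are taken at baseline, three months and six months after inclusion, in line with a horizon described as "with a time horizon of six months".
- **Indirect costs (Economic evaluation).** Besides strategy costs, healthcare costs and production losses, there is a further category that "will be measured for both groups related to the severity of anxiety and depressive symptoms, level of functioning, experience with care, and quality of life".

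**The concern.** The comparator defines what a cost-effectiveness ratio means. Against usual care, training and feedback are part of the added cost, and whatever they achieve is part of the added benefit. Against training and feedback, neither is. The aim promises the first comparison and the design delivers the second. A decision-maker who reads the ratio under the stated aim would take it as the value for money of the whole package over ordinary practice, which the trial does not observe.

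Two further features could affect the numerator of the ratio even once the comparator is corrected. The period over which tailoring is costed is not tied to the six-month period over which QALYs accrue. The indirect-cost sentence is loose enough that losses in functioning or quality of life might be given a money value and added to costs, although EQ-5D QALYs already carry them.

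**Working it through.** **Comparator.** The plan gives no economic figure to reproduce, so the check sets out which terms each comparison needs. Write, per patient, T for training and feedback cost, X for tailoring cost, H for other costs and Q for QALYs. Subscript 1 is the tailored arm, 0 the control arm and U usual care.

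| Comparison | Added cost | Added benefit |
|---|---|---|
| Stated aim (versus usual care) | T + X + (H1 − HU) | Q1 − QU |
| Randomised contrast | (T + X + H1) − (T + H0) = X + (H1 − H0) | Q1 − Q0 |

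- HU and QU are not observed in any arm, and the article describes no external or modelled usual-care data. The first row therefore cannot be estimated from this trial.
- T drops out of the second row. Exact cancellation needs the same cost per patient in both arms. Costs are recorded per practice, so a different number of patients per practice would leave a small remainder; hence they largely cancel.
- The two rows differ in both cost and benefit, so neither the size nor the direction of the gap between the two ratios can be derived from the documents.

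**Costing window.** Inputs: tailoring for 12 months (Tailored strategies), QALY horizon of 6 months (Objectives; Secondary outcomes). Assumption: tailoring cost accrues evenly. The ratio to a matched window is months charged ÷ 6.

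| Months of tailoring charged | Ratio |
|---|---|
| 6 | 6/6 = 1.0 |
| 9 | 9/6 = 1.5 |
| 12 | 12/6 = 2.0 |

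The two-monthly calls give the same answer: 12/2 = 6 calls in the year against 6/2 = 3 in six months. The multiplier applies to X only, not to the whole cost difference X + (H1 − H0). If costs are concentrated early (the interview and first expert advice) and the matched window is the first six months, the ratio falls below 2.0.

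**Indirect costs.** Production losses are already named separately in the same sentence, so the indirect costs read as an extra category. Their listed correlates include functioning and quality of life, which EQ-5D also reflects. Statistical analyses says that direct and indirect costs are reported, but not which of them enter the ratio. If a money value for these states were added to the numerator, the same health change would appear in both numerator and denominator. The text does not say that this will be done.

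**The case against.** The strongest reply is that only a label is wrong. The Economic evaluation section defines the contrast between the randomised groups and Statistical analyses names incremental ratios, so the number produced would be the right one for the design. That stands, and it limits the consequence: a reader might infer that the efficiency result itself will be miscalculated, and the methods text does not support that. It does not remove the point, because the aim governs how the result is described and used.

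Other stronger readings also fail.

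- **Full-year costs will be charged to six months of QALYs.** The article sets no window, and the six-month horizon can be read as limiting costs too. The abstract says measures are taken after the intervention has started, so tailoring before a patient's inclusion may contribute to that patient's outcome. Trimming costs to the same six months could then understate them. The direction of any error is open.
- **Health effects will be double counted.** The sentence says only that such costs are measured, and could mean costs analysed by those outcomes. It is a risk, not a stated method.
- **Listing training and feedback costs is an error.** It is not; they belong in both arms and largely cancel.
- **Two average ratios will replace the incremental one.** The phrase "compare the cost of the QALY gains in each group" is loose, but the same section opens with a difference between groups and Statistical analyses names incremental ratios. It needs tidying only.
- **Practice costs will be spread over too few patients.** The article states no apportioning rule, and the practice questionnaire collects practice population size, not the number of eligible patients. No size can be put on this.

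**Conclusion.** The point holds for the comparator. The stated aim contradicts the design, and the trial can estimate only the cost-utility of tailoring added to training and feedback. This rests on the text alone and needs no assumption. Its numerical effect is not computable because the documents give no costs and no usual-care data.

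The costing window is a secondary point supported by inference: a factor of 1.0 to 2.0 on the tailoring cost component, under even accrual, depending on how much of the year is charged. The indirect-cost sentence is a secondary ambiguity with a possible, not certain, double count. None of this touches the primary outcome or its analysis.

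**What to change.** 1. In Objectives, restate the economic aim as tailoring plus training and feedback versus training and feedback alone, from a societal perspective over six months.
2. Report the incremental ratio for that contrast, with training and feedback costs entered in both arms. Make no claim against usual care unless it is labelled as modelled and its inputs are given.
3. State the period over which tailoring is costed and how tailoring before a patient's inclusion is treated. Show the alternative window as a sensitivity analysis.
4. State that valued health effects (severity, functioning, experience with care, quality of life) do not enter the numerator of the ratio, and say what the indirect-cost sentence is meant to cover.
5. Reword the final step of the cost-utility analysis to match the incremental ratio in Statistical analyses.

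The cost is a few sentences and one extra analysis. No new patient data are needed. The tailoring contacts are already reported under the protocol, so the window analysis is feasible provided those reports record dates and hours, which the article does not state.

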### Time frame

This study was initiated in 2009 and is planned to take 3.5 years.

### Study design

A cluster RCT with two arms has been chosen for this study. Cluster randomisation was applied at the level of the general practice organisation. The general practice organisations were allocated to the intervention or the control group. The allocation was generated by an independent statistician.

The chosen implementation strategies are

1. an educational intervention targeted at GPs, comprising of one day of training at the start and one feedback at six months (in both study arms);

2. one or more interventions tailored to prospectively identified barriers in the local context of GPs (only in the intervention arm).

### Recruitment of general practitioners

We aimed at recruiting patients and GPs in 22 general practices into our trial. Therefore, we prepared a newsletter for GPs with information about the goals of the study; the activities; and the accreditation they would receive if they followed the one-day training in guideline recommendations for the early recognition, diagnosis, and stepped-care treatment allocation of patients with anxiety or depressive disorders. Several recruitment strategies were carried out: (a) the newsletter was published at the website of the Dutch GPs association and the website of the Trimbos Institute, a centre of expertise on mental health and addiction and (b) the newsletter was sent to a sample of 500 GPs, provided by the Netherlands Institute for Health Services Research (NIVEL) and to all GPs who had a contract with a specific health insurance company that gives financial support. Subsequently, a researcher contacted all practices by phone to recommend participation. Finally, 23 general practices were included.

### Recruitment of patients

We aimed at including patients with symptoms that might indicate anxiety or depressive disorders. A sample of patients who visit their GP from September 2010 will receive an information letter with an invitation to participate and will be asked to fill out a short screening instrument: the extended Kessler-10 (EK-10). The Dutch EK-10 is a validated screening instrument for anxiety and depressive disorders in primary care [35]. Of those patients who return the EK-10 and give informed consent to call for the provision of further information about the study, the score on the EK-10 will be calculated. Patients are considered screen-positive if the score is 20 or higher and/or they ticked at least once a 'yes' on the added questions 11 through 16. Screen-positive patients will be called and given further information about the study. Patients who do not meet the exclusion criteria will receive a second information letter, the baseline questionnaire, and a second informed consent form. Patients will be given the option to complete the questionnaire in writing or digitally. Inclusion in the study will be definite if the patient returns the baseline questionnaire and gives informed consent for participation in the study. GPs are not informed about the inclusion of their patient. Figure 1 shows a flowchart of participating patients.

**Figure 1 F1:**
[figure not shown]
**Flowchart of participating patients**.

